| Blood biochemistry                                    |                                   |                                        |                                                                   |                                           |                                            |                                        | *Sub-sample                               |          |                                   |                                        |
| Full blood count                                      |                                   |                                        |                                                                   |                                           |                                            |                                        | *Sub-sample                               |          |                                   |                                        |
| Blood drug levels                                     |                                   |                                        |                                                                   |                                           |                                            |                                        | *Sub-sample                               |          |                                   |                                        |
| Immunology                                            | X                                 |                                        |                                                                   | X                                         |                                            |                                        |                                           | X        |                                   |                                        |
| Peripheral malaria microscopy and PCR                 | X                                 |                                        |                                                                   | X                                         |                                            |                                        |                                           | X        |                                   |                                        |

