### 9.2.2 Safety outcomes

- 1. Severe cutaneous skin reaction in the mothers within 30 days of drug intake
- 2. Other serious adverse events in the mothers
- 3. Congenital malformations identified by six weeks after birth
- 4. Neonatal jaundice within 24 hours and at seven days
- 5. Laboratory test results outside of normal range

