#### 16.1.2 Baseline assessment

A baseline assessment will be conducted for each participant comprising demographic information, socioeconomic information, insecticide treated net (ITN) and indoor residual spraying use, medical and obstetric history, and clinical assessment. Any relevant information already collected during the screening process or at previous antenatal appointments for the same pregnancy will be copied from the antenatal cards onto the CRF, so that questions, tests and examinations are not unnecessarily duplicated.

Study-relevant information recorded at the first visit will include age; area of residence; prior use of ITNs; number of previous known pregnancies and number of previous births. Clinical assessment will include height and weight, fundal height, reported date of last menstrual period and estimated gestation.

A 5 ml venous blood sample will be taken and used for both routine and study-specific testing. This will be obtained after consent for eligibility screening has been obtained but before consent for enrolment in the trial; women who have not been tested for HIV in their current pregnancy will be tested for HIV, and all women will be tested for anaemia and haemoglobin levels. Women not previously tested for syphilis in this pregnancy will be tested and treated if positive. The same blood sample will be prepared for later study-specific testing for malaria (blood smear microscopy and PCR), for markers of immunity to *P. falciparum* malaria, and for markers of iron deficiency. Aliquots of separated blood plasma will be stored at -20 or -80C for immunity studies. A filter-paper sample will be prepared and stored for future research if the woman has given her consent for this.

If not already done, an ultrasound scan will be done at this visit or at a separate visit within a month of enrolment.

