#### **16.4.2 Routine antenatal care and treatment of illness**

Routine antenatal care and treatment of any illness identified at this visit will be provided as described in section 15.2.

As part of routine care, all women will have their haemoglobin levels tested at point of care. Women found to be anaemic ( $Hb \leq 11 \mu g/L$ ) will be treated as appropriate. All women will also be re-tested for HIV, as recommended in the latest WHO guidelines. This will be obtained for a single venous blood draw with additional study-specific testing as described in section 16.4.4.

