## **16.6 Two week post-treatment visit (RDT-positive women treated with DHA-PQ only)**

Women treated with DHA-PQ will be asked to return to the clinic 14 days after the first dose is given. A venous blood sample will be taken for testing of blood DHA-PQ levels, full blood count (red blood cell count, white blood cell count, differential blood cell count); blood haemoglobin levels; and biochemistry (bilirubin, alanine aminotransferase and creatine) for later analysis.

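### Day-14 laboratory results after DHA-PQ are scored only as out of range and not linked to a pre-dose value, so new abnormalities cannot be told from existing ones

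*Combined protocol and SAP*

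**What the plan says.** The visit table in protocol section 3.2 has rows for "Blood biochemistry" and "Full blood count". Each is marked in one column only, the clinic visit 14 days after treatment, and the footnote limits it to ISTp women treated with DHA-PQ. Section 16.6 agrees: "Women treated with DHA-PQ will be asked to return to the clinic 14 days after the first dose is given". The sample is for drug levels, full blood count, Hb and "biochemistry (bilirubin, alanine aminotransferase and creatine) for later analysis".

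Section 9.2.2 lists the laboratory safety outcome in one line: "Laboratory test results outside of normal range". It names no reference range, baseline, grading or change rule, and section 17.3.4 on the safety analysis adds none.

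Hb is handled differently elsewhere. At booking, section 16.1.2 says "all women will be tested for anaemia and haemoglobin levels", on blood drawn before enrolment. At the last scheduled visit, section 16.4.2 says "all women will have their haemoglobin levels tested at point of care". The table shows no Hb at interim visits. Neither section mentions use of these values as a baseline for day 14.

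**The concern.** Every woman sampled at day 14 had tested RDT-positive two weeks before. Section 4.1 links malaria infection to maternal anaemia. Sections 8.2 and 10 exclude only Hb of 7 g/dL or less, so milder anaemia is enrolled. A single level after treatment, read against a normal range, mixes what was there before the first tablet with what appeared after it. It also misses a fall that stays within the range.

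Section 7.2.11 says that DHA-PQ has been studied less than SP for safety in pregnancy and presents the day-14 tests as a contribution to that evidence. An out-of-range percentage with no baseline adds little and is easily misread once published.

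One rule in section 17.3.4 could make this worse. Adverse events with no onset date are treated as treatment-emergent. An abnormality first seen at day 14 has no known onset, so if it were recorded as an adverse event without a date, it would fall under that default. The plan does not say whether laboratory findings are recorded this way.

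**Working it through.** **1. Number of women concerned.** Section 7.2.11 gives about 776 women in the ISTp arm, of whom 20% to 30% are treated: 776 × 0.20 = 155.2 and 776 × 0.30 = 232.8. The stated 155 to 233 is reproduced. (Half of the 1655 in section 17.1 is 827.5, which would give about 166 to 248; this does not change the argument.)

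**2. Which analytes have a value at the visit when treatment starts.**

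| Analyte | Booking | Interim | Final antenatal | Day 14 | Comparator at day 14 |
|---|---|---|---|---|---|
| Hb | all women | none scheduled | all women | treated women | none |
| Bilirubin, alanine aminotransferase, renal marker | none | none | none | treated women | none |
| Red, white and differential counts | none | none | none | treated women | none |

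So Hb can be paired within the same visit for courses started at booking or at the final visit. A course started at an interim visit has only an earlier Hb, from booking or from an unscheduled visit (section 16.7 measures Hb there). The other analytes cannot be paired at all.

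**3. Size for Hb under no drug effect.** The documents give no pre-dose anaemia rate in RDT-positive women. Assume 30% to 70% have Hb of 11 g/dL or less (the anaemia cut-off in section 9.2.1), that all of it persists to day 14, and that this cut-off is what out of range means.
- Low end: 0.30 × 155 = 46.5, about 47 women.
- High end: 0.70 × 233 = 163.1, about 163 women.

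**4. Size for any analyte.** Let b be the share out of range before dosing, r the share of those still out of range at day 14, and q the share of the others who become abnormal. The observed share is b·r + (1 − b)·q, and the pre-existing part of it is b·r divided by that sum. All three inputs are assumed: b from 5% to 40%, r from 50% to 100%, q from 2% to 5%.
- Lowest observed: 0.05 × 0.5 + 0.95 × 0.02 = 0.044, about 7 of 155 or 10 of 233.
- Highest observed: 0.40 × 1 + 0.60 × 0.05 = 0.43, about 67 of 155 or 100 of 233.
- Smallest pre-existing share: 0.025 / (0.025 + 0.0475) = 34%.
- Largest pre-existing share: 0.40 / (0.40 + 0.012) = 97%.

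The day-14 data alone cannot show where in the 34% to 97% range the truth lies.

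**5. Precision of paired Hb change.** The half-width of a 95% interval is 1.96 × SD / √n, with an assumed SD of change of 0.8 to 1.2 g/dL.
- All treated women paired: 1.96 × 0.8 / √233 = 0.10 to 1.96 × 1.2 / √155 = 0.19 g/dL.
- Half paired (78 to 117 women, an assumption, since the plan does not say how many courses start at interim visits): 1.96 × 0.8 / √117 = 0.15 to 1.96 × 1.2 / √78 = 0.27 g/dL.

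These figures describe how precisely the change is measured, not its cause.

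**The case against.** The plan limits its own claims. Section 7.2.11 says too few women will be treated for a useful analysis of sub-clinical effects and points to a larger treatment trial with laboratory testing. Section 7.2.11 also explains why the three drug-exposure groups cannot be compared without bias. The outcome is one of five on safety, with no hypothesis test and no stopping rule attached. This stands, and it keeps the point minor. It does not justify the scoring rule: small numbers are no reason to ignore a baseline already collected.

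Three stronger readings are tempting, and the documents do not support them.
- A reader might infer that out-of-range results will be counted as caused by DHA-PQ. No section says so. Section 9.2.2 only lists the outcome, and section 18.2 has the investigator and the safety monitor judge the causality of adverse events.
- A reader might infer that no pre-dose value exists for anything. That is wrong for Hb.
- A reader might infer that malaria brings liver or kidney abnormalities in these women. The background supports the link to anaemia only, describes most infections as silent or mild, and renal disease is among the exclusions in section 8.2.

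It is also fair to object that pairing does not isolate the drug. Between the treatment day and day 14, parasites are cleared, women may be on iron (sections 10 and 15.2.1), gestation advances, and low values regress to the mean. Pairing removes pre-existing abnormality and no more.

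**Conclusion.** The point holds in a limited form. As defined, the laboratory outcome cannot separate abnormalities present before DHA-PQ from new ones. For chemistry and blood cell counts this follows from the sampling schedule. For Hb it is only a missing link in the analysis, because the pre-dose measurement is already planned.

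The count of 47 to 163 women concerns Hb alone. It rests on an assumed 30% to 70% pre-dose anaemia rate, on full persistence to day 14, and on 11 g/dL or less being out of range; some anaemia would resolve under treatment and lower it. The 34% to 97% range also rests on assumed rates. What does not depend on these assumptions is that the planned outcome provides no means of telling the two sources apart. The primary analyses are not affected.

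**What to change.** **Hb.** Redefine the outcome as change from the pre-dose value, plus the number of women with new or worsened anaemia, and state the cut-offs. Use the same-visit Hb for courses started at booking or at the final antenatal visit. Report courses started at an interim visit separately, against the most recent earlier Hb. State that the change, without a comparator, also reflects parasite clearance, iron treatment and advancing gestation. The cost is analysis wording only.

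**Biochemistry and other cell counts.** Report the day-14 results descriptively with the reference ranges used, and state that they cannot be read as treatment-emergent. This also costs only wording.

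**Optional.** A pre-dose chemistry panel could be run on blood already drawn at booking or the final visit, if volume, stability and consent allow. This is not free. The booking sample is already shared among several tests, and section 16.1.2 commits the plasma to another use: "Aliquots of separated blood plasma will be stored at -20 or -80C for immunity studies". Repeat courses each need their own baseline, interim-visit courses would still have none from the same day, and white-cell and differential counts cannot be recovered from stored plasma.

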## 4 Background

### 4.1 Malaria in pregnancy

Pregnancy increases a woman's susceptibility to malaria infection, with those living in rural areas, in their first or second pregnancy, infected with HIV, and adolescents at particularly high risk. In endemic countries with stable malaria transmission, such as Malawi and much of sub-Saharan Africa, most malaria infections in pregnant women remain asymptomatic or have only mild symptoms, and are therefore undetected and untreated. Symptomatic or asymptomatic falciparum malaria infection affects the placenta and is associated with unfavourable outcomes for both mother and baby, including maternal anaemia, low birth weight (due to intra-uterine growth retardation or pre-term birth) and an increased risk of neonatal death. There is also increasing evidence that babies born to mothers with placental malaria infection are at increased risk of malaria infection in their first and second years of life, and anaemia. Placental malaria has also been associated with reduced mother to child transfer of protective antibodies to infectious diseases such as measles. The control of malaria in pregnancy is therefore important for the health of mothers and babies and an important element of antenatal care in endemic areas. The World Health Organization (WHO) currently recommends three strategies to control malaria in pregnancy; case-management of symptomatic malaria; providing insecticide-treated bed nets (ITNs) to reduce exposure to infective mosquito bites; and intermittent preventive treatment of malaria in pregnancy (IPTp).

### 4.2 Intermittent preventive treatment in pregnancy with sulphadoxine-pyrimethamine (IPTp-SP)

Intermittent preventive treatment in pregnancy (IPTp) is currently recommended for HIV-negative women in all areas with stable moderate to high transmission of malaria. The strategy consists of administration of treatment doses of an efficacious antimalarial drug at predefined intervals at least a month apart during the second and third trimesters of pregnancy, regardless of the presence of malaria parasitaemia. The most common policy is to provide two doses as part of routine antenatal care, but some countries provide three doses. The strategy is thought to work by providing intermittent clearance or suppression of parasites in the placenta, and preventing new infections from occurring.

Sulphadoxine-pyrimethamine (SP) is the only drug currently used for IPTp. It has a profile that makes it highly suitable for this use. SP is very well tolerated and safe in the second and third trimester of pregnancy for mother and foetus. SP is also widely available, cheap, and can be given as a single dose.

IPTp-SP is not recommended for HIV-positive women. WHO recommends that HIV-positive women receive co-trimoxazole prophylaxis for HIV-related infections. Because co-trimoxazole and SP are both sulpha-containing drugs, SP is contra-indicated in HIV-positive women receiving co-trimoxazole. However, co-trimoxazole itself has some antimalarial properties and therefore serves to protect pregnant women with HIV infection from malaria infection.

### 4.3 Effectiveness of IPTp-SP in the context of increasing SP resistance

Increasing SP resistance is now a major challenge to IPTp-SP efficacy and effectiveness. Because of widespread and increasing resistance to SP, almost all countries in eastern and southern Africa have now switched their first-line treatment for symptomatic malaria to an artemisinin based combination therapy (ACT), as recommended by WHO. A previous meta-analysis showed that IPTp with SP remains effective even in areas where SP fails in approximately one third of treatments of symptomatic children with malaria by day 28. SP therefore continues to be used for IPTp in many countries where it is no longer used for treatment of symptomatic malaria, because it has maintained efficacy for this purpose.

However, there is now evidence from a recent study in northern Tanzania that IPTp-SP may no longer be effective at higher rates of resistance, and may even be harmful in the context of very high resistance. In this study IPTp use was associated with increased (rather than decreased) placental inflammation and levels of parasitaemia in malaria-infected pregnant women carrying parasites with the SP resistance mutation *dhps* 581. This supports a hypothesis that the most highly resistant parasites out-compete by having a relative fitness advantage and can overgrow less resistant parasites under drug pressure. The use of SP for IPTp in settings of widespread high SP resistance may therefore actually exacerbate malaria infections and further increase SP resistance.

### 4.4 SP Resistance and declining effectiveness of IPTp-SP in Malawi

Malawi was the first country to introduce IPTp-SP in 1993, and the strategy initially appeared effective. Monitoring by the Queen Elizabeth Central Hospital in Blantyre showed that between 1997 and 2006 the prevalence of placental malaria detectable by microscopy decreased five-fold from 21.2% to 4.2% in first pregnancies and ten-fold from 18.9% to 1.9% in second and subsequent pregnancies. At the same time there was a steady increase in ITN use from 18% to 60%; while IPTp-SP use increased from around 20% in 1997 to 78% in 2002, but dropped again to less than 50% by 2006, suggesting that the increased use of ITNs was responsible for the continued fall of placental malaria rates.

The same study observed that the effectiveness of IPTp-SP in Malawi appeared to reduce dramatically between 2002 and 2006, to the extent that it may no longer be protective. After 2002, women who received two or more doses of IPTp-SP were equally likely to have placental malaria, anaemia, or low birth weight babies compared to women who had not received any IPTp. During the same period, ITNs were strongly associated with higher birth weights and decreased infection rates.

These findings are consistent with an increasing impact of SP resistance on IPTp effectiveness. The degree of SP resistance in 2001-2004 was high; over 90% of parasites had the 'quintuple mutant' (*dhfr* mutations N511, C59R and S108N, and *dhps* mutations A437G and K540E) associated with SP resistance. However, previous trials have also shown that IPTp-SP provides less benefit in women who are also protected by ITNs; therefore the reduced efficacy of SP probably reflects the combination of high concurrent ITN use and high levels of SP resistance.

#### 4.5 Economics of malaria in pregnancy

To date only limited data are available on the economic impact of malaria in pregnancy. To capture adequately the economic burden of malaria in pregnancy and conduct a high quality cost-effectiveness analysis, good epidemiological data, including the effects on the mother and offspring, the costs associated with prevention and treatment, and a better understanding of the long-term health and economic consequences are needed.

To date there are three published cost-effectiveness analyses on malaria in pregnancy interventions in Malawi, with two comparing presumptive treatment with chloroquine versus SP and one comparing different health education messages to improve compliance to chemoprophylaxis. None of them took any costs incurred by households into consideration.

A review conducted by Worrall et al found IPTp-SP to be relatively cost-effective or highly cost-effective in all studies conducted in sub-Saharan Africa, but this is likely to be affected by the falling transmission, by the coverage of ITNs and by the increasing resistance of *P. falciparum* to SP. In the context of scarce resources it is important to assess the cost-effectiveness, affordability, feasibility and implementability of the proposed intervention in addition to its efficacy and effectiveness.

### 5 Rationale: Alternative approaches to IPTp-SP in the context of declining effectiveness

The problem of declining IPTp effectiveness now urgently needs to be investigated and studies of alternative approaches to IPTp-SP considered. The two possible options for consideration are replacing SP with other drugs for IPTp, and alternative strategies to replace IPTp.

## 5.1 Alternative drugs for IPTp

A series of studies is looking into alternative drugs that could replace SP for IPTp. A study in Benin showed mefloquine to be more efficacious than SP for preventing placental malaria, clinical malaria, and maternal anaemia at delivery. A study in Ghana showed IPTp with amodiaquine or a combination of amodiaquine and SP to have comparable effects to SP. Further studies comparing IPTp-SP and IPTp using mefloquine (MiP Consortium) and with azythromycin-chloroquine are ongoing in Africa and the results will be available in the next three to four years. None of these new IPTp candidates, however, have the same favourable profile as SP; they are more complicated to give (azithromycin-chloroquine and amodiaquine-based regimens need to be taken once daily for three days, compared with a single dose for SP) and are not as well tolerated, which are important considerations in a strategy that targets otherwise healthy asymptomatic women.

Furthermore, malaria transmission among pregnant women has reduced considerably in southern Malawi and is likely to decline further following increased control measures including indoor residual spraying (IRS), widespread ITNs and use of ACTs in the community (ACTs kill gametocytes and can therefore help reduce transmission). This reduces the number of women at risk of malaria and the potential impact and cost-effectiveness of presumptive approaches such as IPTp. The marked reduction in exposure risk and the need for change to an alternative drug regimen has changed the risk-benefit profile for IPTp. Under these circumstances, intermittent screening and treatment in pregnancy (ISTp) provides a potential alternative strategy that is increasingly being considered.

